# Optimizing home-based long-term intensive care for neurological patients with neurorehabilitation outreach teams – protocol of a multicenter, parallel-group randomized controlled trial (OptiNIV-Study)

**DOI:** 10.1186/s12883-022-02814-y

**Published:** 2022-08-04

**Keywords:** Neurorehabilitation, Weaning, Clinical trial, Protocol, Healthcare

## Abstract

**Background:**

Even with high standards of acute care and neurological early rehabilitation (NER) a substantial number of patients with neurological conditions still need mechanical ventilation and/or airway protection by tracheal cannulas when discharged and hence home-based specialised intensive care nursing (HSICN). It may be possible to improve the home care situation with structured specialized long-term neurorehabilitation support and following up patients with neurorehabilitation teams. Consequently, more people might recover over an extended period to a degree that they were no longer dependent on HSICN.

**Methods:**

This healthcare project and clinical trial implements a new specialised neurorehabilitation outreach service for people being discharged from NER with the need for HSICN. The multicentre, open, parallel-group RCT compares the effects of one year post-discharge specialized outpatient follow-up to usual care in people receiving HSICN. Participants will randomly be assigned to receive the new form of healthcare (intervention) or the standard healthcare (control) on a 2:1 basis. Primary outcome is the rate of weaning from mechanical ventilation and/or decannulation (primary outcome) after one year, secondary outcomes include both clinical and economic measures. 173 participants are required to corroborate a difference of 30 vs. 10% weaning success rate statistically with 80% power at a 5% significance level allowing for 15% attrition.

**Discussion:**

The OptiNIV-Study will implement a new specialised neurorehabilitation outreach service and will determine its weaning success rates, other clinical outcomes, and cost-effectiveness compared to usual care for people in need for mechanical ventilation and/or tracheal cannula and hence HSICN after discharge from NER.

**Trial registration:**

The trial OptiNIV has been registered in the German Clinical Trials Register (DRKS) since 18.01.2022 with the ID DRKS00027326.

## Background and objectives

### Background

A considerable proportion of patients with acute neurological conditions, such as stroke or traumatic brain injury (TBI), suffer from persistent disorders of consciousness (DoC), deficits of autonomic drive for breathing, severe paresis, and/or dysphagia (deficits of swallowing functions), severe enough to necessitate tracheostomy and use of a so called blocked tracheal cannula (preventing aspiration and aspiration pneumonia) and/or mechanical ventilation [1, 2]. Similarly, patients with conditions requiring prolonged intensive care unit treatment including ventilation support frequently acquire secondary neurological deficits of the central and peripheral nervous system as well as muscles with motor, sensory, and cognitive deficits and frequently emotional disorders, a syndrome called Post Intensive Care Unit Syndrome, PICS [3, 4].

Neurological early rehabilitation (NER) is the treatment of choice for this group of patients, promoting stabilization of organ function by intensive care treatment while at the same time reducing functional deficits based on an interdisciplinary rehabilitation team approach [5]. This type of treatment is rather successful. In a German cohort, 26% of 754 patients were mechanically ventilated at the time of admission to NER; their rate of weaning from mechanical ventilation was 65% during inpatient care in NER [6]. More recently, 36 weaning units in early neurological rehabilitation from 11 federal states in Germany with a total of 496 beds participated in another survey [7]. From 2516 weaning cases documented in 2019, 2097 (83.3%) could primarily be successfully weaned from mechanical ventilation and only 120 (4.8%) had to be discharged with home ventilation support.

Furthermore, a recent Germany-wide survey documented considerable hospital capacities (“beds”) for prolonged weaning from a mechanical ventilator for patients with neuro-disabilities [8]. Sixty-eight institutions declared to have such capacities with a broad distribution across Germany and its federal states. Overall, 1094 “beds” for prolonged weaning (and neurorehabilitation) were reported.

While effective treatment and capacities for such specialised healthcare is available in Germany (and other countries), there is still a substantial proportion of patients, who need mechanical ventilator support and/or airway protection by a (blocked) tracheostomy tube at discharge from neurological early rehabilitation. These patients will then need continuous (24/7) home-based specialized intensive care nursing with skilled staff being present to deal with any medical problems that might arise and need instantaneous reaction. In Germany, this form of out-of-hospital intensive care support can be provided in the patient´s home, in specialized long-term care facilities, or in shared apartments, where up to 6 patients can be cared for.

Given the demographic changes of societies and progress in survival rates of people receiving prolonged intensive care unit (ICU) treatment, the absolute numbers of people with need for home-based specialized intensive care nursing is rising considerably. Indeed, the number of people in need for invasive long-term ventilation in Germany dramatically increased over the past 15 years to an estimate of 20.000 patients in 2019, implying additional healthcare cost of around 4 billion Euros per year [9].

### Objectives and hypotheses

Neurological conditions frequently take a long time to recover and recovery can be promoted for prolonged periods by trained staff from various medical disciplines, e.g. medical doctors, therapists from various professions, and nurses trained in neurorehabilitation, most efficiently organized as interdisciplinary teams [10].

Inpatient NER is effective and beneficial for many neurological patients, because it has the key element of interdisciplinary, goal-oriented, and frequently adapted therapy and monitoring within a multi-professional team that is in constant communication [11, 12]. Long-term community-based care of neurological patients is often lacking these key elements of successful patient-centered care: involved and experienced physicians, nursing staff, and therapists are often highly motivated and provide excellent care, yet there is little coordination and communication between these different stakeholders and a lack of common patient-centered goals. A multi-professional team approach and combining efforts to improve functioning, activities, and participation seem, however, to be crucial for long-term outcome in neurorehabilitation [11, 12].

In such an situation, it might well be that if the sectorial healthcare borders and hence barriers for specialized long-term treatment were overcome that more people might recover over an extended period to a degree that they were no longer dependent from mechanical ventilation and were no longer in need for airway protection by blocked tracheal cannulas (via tracheostomy). If that could be achieved, the number of people requiring HSICN could be reduced.

This healthcare project and clinical trial “OptiNIV” (acronym for optimizing post-discharge intensive care for neurological patients) is set forth to:Implement specialized post-discharge follow-ups by out-patient neurorehabilitation teams based at specialized neurorehabilitation hospitals for people with a long-term need for mechanical ventilation and/or tracheal cannula and hence for HSICN in the federal state of Bavaria (Germany)Provide individualized managed care and treatments plans tailored to improve neurological functioning to healthcare professionals in charge at the community levelImplement structured short inpatient assessments at neurorehabilitation hospitals to identify patients, who are ready to be weanedImplement a period of secondary inpatient rehabilitation to achieve weaning from mechanical ventilation and/or tracheostomy tube in patients assessed to have this potentialAnd to test with a parallel-group randomised controlled trial, RCT the superiority hypothesis that such a specialized outreach healthcare service increases the rates for weaning from mechanical ventilation and/or decannulation (and promotes other clinical and economic outcomes) within the first year post discharge from neurological early rehabilitation.

## Methods

### Trial design and characteristics

#### Design

This superiority trial is a multicentre, open, parallel-group RCT, which compares post-discharge specialized outpatient follow-ups by neurorehabilitation teams to usual care for people with a need for mechanical ventilation and/or tracheal cannula and hence for HSICN after discharge from NER. The RCT has the objective to assess effects of the specialized outreach healthcare service on rates for weaning from mechanical ventilation and/or decannulation and other clinical and economic outcomes within the first year post discharge.

#### Settings and locations

The study is implemented by a network of 12 cooperating centres of neurological early rehabilitation in the federal state of Bavaria (Germany) (compare Fig. 1) recruiting eligible patients at discharge from their service. These 12 centers provide full coverage of the population of approximately 13 million in Bavaria (www.statistikdaten.bayern.de).

**Fig. 1 Fig1:**
[figure not shown]
The 12 participating centres of the trial, the study coordination centre in Munich, and the scientific evaluation centres in Greifswald. ■ Study coordination centre: Department of Neurology, University Hospital, Ludwig-Maximilians-University Munich. ○ Regional Outreach Centres, ROC: Schoen Clinic Bad Aibling Harthausen; Therapy Centre Burgau; Clinic for Neurology of the University of Regensburg at medbo district hospital; Clinic for Neurological Early Rehabilitation/Intensive Care, Rhön-Klinikum, Campus Bad Neustadt. △ Participating Neurological Early Rehabilitation centre, NER: Juliusspital Würzburg, VAMED Klinik Kipfenberg, Schoen Clinic Bad Staffelstein, m&i Fachklinik Enzensberg, m&i Fachklinik Herzogenaurach, m&i Fachklinik Bad Heilbrunn, Neurological Centre at the Bezirksklinikum Mainkofen. ● Independent scientific evaluation centres in Greifswald: Greifswald University Medical Center; University of Greifswald. Source maps offered by [name] were obtained from Inmagine Lab Pte. Ltd ("123RF") with a license to use and adapt it

Four of these centres provide the regional post-discharge specialized outpatient follow-ups with neurorehabilitation teams and constitute the “regional outreach centres” (ROC), resulting in a division of the federal state into four regions (North, East, South, West). Each ROC is responsible to establish the new healthcare service in its region.

Another study setting is the participants’ residences, where they receive the HSICN.

#### Trial status

Participant recruitment was planned to start in 2022. At the time of submission of this manuscript, the first patients have been enrolled.

### Participants

#### Eligibility criteria

Subjects aged 18 years or older with acute neurologic conditions (onset < 6 months ago), who are transferred to HSICN after completion of inpatient NER and who are still mechanically ventilated and/or cannulated will be included. When post-discharge weaning from mechanical ventilation and/or decannulation appears to be medically precluded or when life expectancy is less than 12 months candidates are not eligible for the trial. The detailed inclusion and exclusion criteria are given in Table 1.

**Table 1 Tab1:** Inclusion and exclusion criteria

Inclusion criteria
1. Age ≥ 18 years
2. Health insurance with AOK Bayern
3. Inpatient neurological early rehabilitation with a neurological rehabilitation diagnosis
4. Mechanical ventilation and/or tracheal cannula
5. (Sub-)Acute medical condition (onset < 6 months before study entry)
6. Planned discharge to home-based intensive care
7. Informed consent for study participation
**Exclusion criteria**
1. Palliative treatment/life expectancy < 12 months (according to medical assessment)
2. Weaning/decannulation prospectively medically excluded (e.g., high cervical paraplegia, laryngeal tumor)
3. Preexisting home-based intensive care
4. Progressive neuromuscular disease (e.g., muscular dystrophy, ALS)
5. Home-based intensive care by a team already providing care to OptiNIV study participants

#### Screening

Screening will primarily take place in the 12 NER hospitals. The first patient was enrolled in March of 2022 and recruiting will continue through the middle of 2023. In addition to the hospital-based recruitment in participating centres, the AOK Bavaria (public health insurance) will support recruitment of eligible persons treated in and discharged from other hospitals in Bavaria.

#### Recruitment and baseline assessment

After assessing eligibility, detailed information will be provided to the patient and/or his/her legal guardian by physicians of the 12 NER hospitals, and written consent to study participation will be obtained ("informed consent"). Afterwards, the baseline visit (t_0_) will take place at the NER hospital prior to discharge to HSICN. As part of this, demographic and clinical data are collected as well as information on the participant’s mechanical ventilation and tracheostomy status, use of other medical devices, health status and quality of life by using questionnaires and checklists (Table 2). The visit will be carried out by trained site personnel and the results will be recorded in case report forms (CRF).

**Table 2 Tab2:** Outcome measures and assessment schedule

		**Study period**					
		**t**_**0**_	**t**_**1**_	**t**_**2**_	**t**_**3**_	**t**_**4**_	**t**_**5**_
**Outcome**	**Assessment tool**	**Baseline**	**Month 1**	**Month 3**	**Month 6**	**Month 9**	**Month 12**
Status tracheal cannula (primary)	Decannulated [Y/N] [Reasons/Checklist) Unblocking time/day [min.] Total duration	x	x	x	x	x	x
Status mechanical ventilation (primary)	Weaned [Y/N] Current weaning stage Total duration	x	x	x	x	x	x
Survival	Death [Y/N] Time to death after discharge		x	x	x	x	x
Medical devices (e.g. PEG tube)	Checklist	x	x	x	x	x	x
Specific neurological medication	Checklist	x	x	x	x	x	x
Global neurological outcome	Glasgow Outcome Scale Extended (GOS-E)	x	x	x	x	x	x
Neurological status: Level of consciousness Degree of paresis Spasticity Dysphagia	Coma Recovery Scale-Revised (CRS-R) Motricity Index (MI) Resistance to Passive Movement Scale (REPAS) Bogenhausener Dysphagie Score (BODS) Penetrations-Aspirations Skala (PAS)	x	x	x	x	x	x
Pain scale	Visual analogue scale (0 – 100)	x	x	x	x	x	x
Activities of daily life	Barthel-Index (BI)	x	x	x	x	x	x
Quality of life (QOL) (Patient and relatives)	European Quality of Life-5 Dimensions (EQ-5D-5L)	x	x	x	x	x	x
Social participation (Patient and relatives)	WHO Disability Assessment Schedule (WHODAS 2.0)	x					x
Depression/anxiety (Patient and relatives)	Hospital Anxiety and Depression Scale (HADS)	x	x	x	x	x	x
Burdens on the relatives (relatives)	Modified Caregiver Strain Index (MCSI)		x	x	x	x	x
Complications (including unplanned hospitalisations)	Semi-standardised free text	x	x	x	x	x	x
Satisfaction with health care situation (Patient, relatives, and home-based intensive care personnel)	10-point Likert scale		x	x	x	x	x
Adherence to the treatment pathway (IG)	[Y/N] Checklist Free text		x	x	x	x	x
Utilisation of healthcare (e.g. HSINC, hospital stays, outpatient medical services, aids)	Checklist AOK Bavaria data		x	x	x	x	x
Costs at the expense of SHI (separated according to sectors, cost types)	Costs per type in Euro [€] (AOK Bavaria)						x
Whereabouts of the patient	Checklist		x	x	x	x	x

*IG* Intervention group, *SHI* Statutory health insurance

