### Intervention

#### Experimental condition

The experimental condition is a new systematic healthcare bundle, primarily based on post-discharge specialized outpatient follow-ups by ROC-based neurorehabilitation teams for people with a need for ongoing mechanical ventilation and/or tracheal cannula and hence for HSICN after discharge from NER. The intervention will provide team-based neurorehabilitation healthcare counselling and support during the first year after discharge from NER that aim at promoting further functional neurological recovery with a focus on breathing and swallowing and consecutively continued weaning from mechanical ventilation and/or promoting a functional status that safely allows decannulation. Teams are physician-led and can include specialized breathing therapists trained to support weaning form mechanical ventilation, dysphagia therapists, physiotherapists, occupational therapists, and/or specialized nursing staff.

Elements of the healthcare bundle are:Team sessions in the ROC to evaluate participants’ data (see 2 & 3), develop and communicate a managed care plan with healthcare recommendations to the HSICN staff, treating physicians and therapists;Continuous exchange of vital data, mechanical ventilation and tracheal cannula management data, as well as laboratory data between the HSICN and the ROC; a telephone hotline is available to HSICN in case of need for advice regarding patient care;Regular patient visits within their HSICN-setting by the ROC-based outreach teams to assess participants’ clinical status personally including blood gas analysis, BGA, and functional swallowing assessment (fiberendoscopic evaluation of swallowing, FEES);Short inpatient re-evaluations in the ROC when a potential for weaning and/or decannulation is observed;Inpatient neurorehabilitation period (couple of weeks) in the ROC when the short inpatient re-evaluation indicated the likelihood of a successful weaning and/or decannulation.

Sequence of events:

As a central part of the experimental intervention, therapy plans for long-term weaning from mechanical ventilation and/or decannulation will be developed in collaboration with outpatient healthcare providers (e.g. general practitioners, physiotherapists, HSICN staff).

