Defined changes of vital signs will trigger the HSICN staff to send the current patient's medical condition reports to the ROC. Based on these reports, the therapy plans and weaning protocols will be updated in interdisciplinary team conferences and will be forwarded to the home-based intensive care staff.

In addition, the intervention includes visits to study participants by outpatient follow-up teams consisting of physicians and therapists dispatched by the ROC. Each ROC has an outpatient follow-up team that covers its region. The visits will start 4 weeks after discharge from neurological early rehabilitation and will continue with visits every three months thereafter for one year. At each visit (t_1_-t_5_) the outpatient follow-up teams perform discipline-specific examinations, including blood gas analysis (BGA) and FEES. Additional visits to the HSICN by the ROC are possible, if needed.

Once the potential for weaning from mechanical ventilation and/or decannulation is considered by the outpatient follow-up team, the study participant will be admitted to the respective ROC. Here, a more comprehensive assessment of the potential for weaning from mechanical ventilation and/or decannulation is conducted as part of a structured diagnostic process over a few days (“Interdisciplinary Inpatient Structured Assessment”, IISA).

If the potential for successful weaning and/or decannulation is confirmed during an IISA, an inpatient neurorehabilitation program with a weaning procedure similar to NER will follow (“Neurological interval rehabilitation”, NIR).

In addition to the above-mentioned experimental intervention aspects the outpatient follow-up teams will document study data at each visit (t_1_-t_5_) (as specified in Table 2).

For compensation to those who suffer harm from the experimental intervention a liability insurance coverage has been established.

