#### Secondary outcomes

Secondary outcomes include the following: Tracheal cannula and ventilatory status and modalities, mortality, neurological status, activities of daily living, quality of life (QOL), depression/anxiety, pain, social participation, burden on the relatives, healthcare situation (use of home-based intensive care, living arrangement), satisfaction with healthcare situation, utilisation of healthcare (medical services, medication, remedies and aids, hospital care), complications/adverse events (including unplanned hospitalisation).

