#### Monitoring and data management

Before recruitment begins, the study centres receive training on the study protocol, use of the assessment instruments, the study documentation, the forwarding of the study documentation to the evaluating institutions, as well as the process and obligations regarding data validation. Video-based and written training material is made available via an access-restricted web site for continuous training purposes. Individual training and delegation of study processes are documented by corresponding logs in investigator site files.

The monitoring is carried out by the central project co-ordination (LMU) and the evaluating institution (UMG) independently of both the funding agency and participating centres and will commence after the inclusion of the first patients, in order to ascertain compliance with the study protocol, and to identify problems and difficulties in the implementation and documentation at an early stage.

After enrolment, patients will receive an identification number as an encryption (pseudonymisation), so that their names will only appear on the informed consent form and a patient identification log, but not on other study documentation. The data collection is realized on the basis of CRFs (Case Report Forms).

The CRFs are forwarded digitally from the recruiting centres or ROC to password-protected cloud areas on servers of the University Medical Center Greifswald responsible for the independent clinical scientific evaluation. The original CRFs remain in the recruiting centres or ROC, respectively.

Subsequently, the evaluating institution will review all CRFs for missing entries, inconsistencies and implausibility, and resolve potential queries with the study teams of the participating centres. Thereafter, CRF-documented trial data will be entered in a digital database and double-checked for correctness.

The AOK Bavaria transmits the pseudonymised data of inpatient treatment to the University of Greifswald (UG) for the health economic evaluation. A trustee agency is responsible for providing a linking between the primary data of the study (as documented on CRFs) and the routine data of the AOK Bavaria.

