#### Methods for additional analyses

The sample size is calculated to test the primary hypothesis for the total study population with sufficient statistical power. It does not provide statistical power for subgroup analyses (assuming effects of a comparable magnitude). Therefore, the planned investigation of interaction effects (subgroup analyses) will only be exploratory.

Additional between-group analyses for secondary outcomes will be performed in an analogous way as stated for primary outcomes.

Associations between patient characteristics and outcomes, or among different outcomes will be analysed by correlational analyses.

Based on the outcomes documented for the health economic analysis utilization and cost comparisons between experimental and control group as well as outcome-related cost-effectiveness analyses will be performed analyzing the relationship between benefit (harm) and cost incurred.

In addition, system dynamics models will be used to assess potential future cost-effectiveness of the intervention for the post-intervention phase.

An interim analysis is not planned.

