### Risk of bias considerations

The study design was chosen to ensure the best possible protection against systematic bias.

Potential selection bias is prevented by the concealed, stratified random allocation of patients to treatment groups in blocks by a partner not involved in recruitment.

No blinding of study personnel, patients or those conducting the evaluation will be possible for the experimental intervention, which increases the potential for performance bias and detection bias. Given the objective nature of the primary outcomes risk of detection bias is, however, considered low for these outcomes.

To reduce potential over- or underestimation of the intervention effect due to study dropouts (attrition bias), an intention-to-treat analysis will be conducted.

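### The between-arm comparison of complications and unplanned hospitalisations is open to ascertainment bias of unknown size and direction, and linked insurance records are not named as its source

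*Protocol article*

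**What the plan says.** **Outcome and comparison.** The Secondary outcomes section lists "complications/adverse events (including unplanned hospitalisation" among the secondary outcomes. Under Methods for additional analyses, "Additional between-group analyses for secondary outcomes will be performed in an analogous way as stated for primary outcomes".

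**Instrument and recorder.** Table 2 gives the row "Complications (including unplanned hospitalisations" one tool, "Semi-standardised free text", at t0 to t5. The Experimental condition section has the ROC outpatient follow-up teams document study data at t1 to t5. The Control condition section sends the same teams to control participants at the same frequency, for data collection only.

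**Contact outside the visits.** The Experimental condition section describes continuous exchange of vital, ventilation, cannula and laboratory data with the ROC, and "a telephone hotline is available to HSICN in case of need for advice regarding patient care". It adds that "Defined changes of vital signs will trigger the HSICN staff to send the current patient's medical condition reports to the ROC". It also allows extra visits, and provides for inpatient assessment (IISA) and interval rehabilitation (NIR) at the ROC where there is potential for weaning. None of this is described for controls.

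**Blinding.** Risk of bias considerations states: "No blinding of study personnel, patients or those conducting the evaluation will be possible for the experimental intervention". It accepts that this raises the potential for detection bias, and calls that risk low for the primary outcomes only.

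**Insurance data.** AOK Bayern membership is an inclusion criterion. Under Monitoring and data management, "The AOK Bavaria transmits the pseudonymised data of inpatient treatment to the University of Greifswald (UG) for the health economic evaluation", and a trustee agency links AOK data to the case report forms (CRFs). Table 2 also names AOK data for the healthcare-utilisation row, which includes hospital stays. No section names AOK data for the unplanned-hospitalisation item.

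**The concern.** An identical form and visit schedule equalise how the question is put, but not what the recorder already knows. For an intervention participant the ROC may hold an event in its own records through the data exchange, the hotline, a triggered report or an inpatient stay. For a control participant the protocol gives the team no such route, so it depends more on what the household and nursing staff report at visits two to three months apart after month 1. Free text is sensitive to this difference, and the recorder knows the arm and has a part in delivering the intervention.

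What is at stake is the reading of one secondary outcome that bears on safety. A difference could reflect recording rather than events, and a true difference could be hidden or put down to better detection. The plan's own reassurance on detection bias does not reach this outcome, and nothing else in the article addresses it.

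**Working it through.** **1. The plan's own figure.** The protocol gives no figure for complications, so the only one to reproduce is the sample size. With 30% vs 10%, 2:1 allocation, two-sided 5%, 80% power, pooled variance and no continuity correction, the result is 49 control + 98 intervention = 147. Then 147 / 0.85 = 172.9, rounded up to 173. Both agree with the Sample size section. The present point does not alter them; they supply only the group sizes used below.

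**2. Sources of knowledge about a complication, by arm**

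| Source available to the ROC | Intervention | Control |
|---|---|---|
| Scheduled visit with the common form | yes | yes |
| Continuous data exchange | yes | not described |
| Hotline from home nursing staff | yes | not described |
| Reports triggered by vital signs | yes | not described |
| Additional visits if needed | yes | not described |
| IISA or NIR stay at the ROC | when indicated | not described |
| AOK inpatient records | yes, linked | yes, linked |

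The last row is the only source in the table that arises independently of the study team. It is not named for this outcome.

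**3. Illustration of size (all rates assumed).** The protocol states neither a complication risk nor any detection rate. Let the true risk be the same in both arms, t, and let the detected proportions be d_I and d_C.

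- Observed risks: t × d_I and t × d_C.
- Apparent relative risk: d_I / d_C, which does not depend on t.
- Chance of a falsely significant excess in the intervention arm: exact binomial enumeration of all outcomes at 98 vs 49, Pearson chi-square at two-sided 5%, counting rejections in that direction only.

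| True risk | Detection, intervention vs control | Observed risks | Apparent RR | False excess |
|---|---|---|---|---|
| 50% | 90% vs 90% | 45% vs 45% | 1.00 | about 2.6% |
| 50% | 90% vs 80% | 45% vs 40% | 1.13 | 8.4% |
| 50% | 90% vs 70% | 45% vs 35% | 1.29 | 21.2% |
| 30% | 90% vs 80% | 27% vs 24% | 1.13 | 5.5% |
| 30% | 90% vs 70% | 27% vs 21% | 1.29 | 11.5% |

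At the recruited 115 vs 58 and 50% true risk, the two unequal settings give 9.2% and 24.3%. A small gap has a small effect: 95% vs 90% at 50% true risk and 98 vs 49 gives 5.0%.

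**4. Masking.** If the true relative risk were 0.80 and detection were 95% vs 75%, the observed value would be 0.80 × 0.95 / 0.75 = 1.01, so a real benefit would not show.

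**5. Direction.** If the unblinded team under-recorded in the arm it treats, say 70% vs 90%, the apparent relative risk under equal true rates would be 0.70 / 0.90 = 0.78. Nothing in the protocol settles which mechanism would prevail.

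**The case against.** Several points on the other side stand.

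- **Design symmetry.** The same team uses the same semi-standardised tool at the same visits in both arms. HSICN participants have round-the-clock nursing staff who can report events, and every visit from t1 also covers healthcare use and whereabouts by checklist. This limits the imbalance, particularly for hospital admissions, and makes large detection gaps hard to support.
- **AOK data are not confined to the economic evaluation.** A reader of the data-management section alone might infer that they are. Table 2 names them for the utilisation row, and utilisation, including hospital care, is itself a secondary outcome. A comparison of hospital stays from claims is thus largely foreseen. What is missing is the link to unplanned hospitalisation.
- **Safety does not rest on this row alone.** Death is a separate yes/no item with time to death in both arms, and serious adverse events go to the co-ordinating centre for evaluation.
- **An SAP may deal with coding and adjudication.** That is so, and their absence here is no finding. Coding cannot, however, recover events that were never recorded, and the instrument and recorder are fixed in this document.

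A reader might also infer that the comparison is biased against the intervention, so that equal true rates would look like more harm. The contact structure suggests that direction, but an unblinded team could also under-record in its own arm. The documents support exposure to bias, not a demonstrated bias of known sign.

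**Conclusion.** The point holds in a limited form. The comparison of complications and unplanned hospitalisations rests on free text from an unblinded team that has extra sources of information in one arm only, and the plan's reassurance on detection bias does not cover it. The comparison is open to ascertainment bias of unknown size and direction. The apparent relative risks of 1.13 to 1.29, and the 5% to 21% chances of a falsely significant excess at 98 vs 49, show what moderate gaps in detection could do. They rest entirely on assumed true risks (30% and 50%) and assumed detection rates, and are not estimates for this trial.

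It would go too far to conclude that the trial cannot say anything about safety: mortality is recorded separately, and hospital stays are already drawn in part from AOK data. The point is worth acting on because a source common to both arms is already being collected and linked.

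**What to change.** 1. Name the linked AOK inpatient records as the source for the between-arm comparison of unplanned hospitalisation, for all randomised participants from discharge to month 12.
2. Predefine a rule that classifies stays as planned or unplanned, apply it without knowledge of arm as far as possible, and report IISA and NIR stays separately. Those are part of the intervention, and would otherwise enter the intervention arm's count.
3. Treat free-text complications in both arms as supportive, and state the unequal contact as a limitation.
4. Do not restrict the comparison to events marked as elicited by the visit question. That would drop intervention-arm events already known through the extra contact, while control events have no such route, and would tilt the comparison the other way.

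**Cost.** Wording in the analysis plan and a classification rule; the data transfer and linkage are already planned. The downsides are small: the analysis waits for complete claims, and inpatient records do not cover complications managed at home, for which free text remains the source. Because the Data Availability section ties data use to purposes agreed in the consent, the sponsor should confirm that the consent covers this use.
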